# Impact of preoperative Vitamin D_3_ administration on postoperative hypocalcaemia in patients undergoing total thyroidectomy (HypoCalViD): study protocol for a randomized controlled trial

**DOI:** 10.1186/s13063-016-1216-5

**Published:** 2016-02-20

**Keywords:** calcitriol, hypocalcaemia, hypoparathyroidism, total thyroidectomy, vitamin D deficiency

## Abstract

**Background:**

Total thyroidectomy is increasingly used as a surgical approach for many thyroid conditions. Subsequently, postoperative hypocalcaemia is observed with increasing frequency, often resulting in prolonged hospital stay, increased use of resources, reduced quality of life and delayed return to work. The administration of vitamin D is essential in the therapy of postoperative hypocalcaemia; calcitriol is most commonly used. What has not been examined so far is whether and how routine preoperative vitamin D prophylaxis using calcitriol can help to prevent postoperative hypocalcaemia. This study evaluates routine preoperative calcitriol prophylaxis for all patients who are to undergo a total thyroidectomy, compared with the current standard of post-treatment, i.e., selective vitamin D treatment for patients with postoperative hypocalcaemia.

**Methods/design:**

This clinical observational (minimal interventional clinical trial) trial is a multicentre, prospective, randomized superiority trial with an adaptive design. Datasets will be pseudonymized for analysis. Patients will be randomly allocated (1:1) to the intervention and the control groups. The only intervention is 0.5 μg calcitriol orally twice a day for 3 days prior to surgery. For the primary endpoint measure (number of patients with hypocalcaemia), hypocalcaemia is defined as serum calcium of less than 2.1 mmol/l on any day during the postoperative course; this measure will be analyzed using a Chi-square test comparing the two groups. Secondary endpoint measures, such as number of days to discharge, quality of life, and economic parameters will also be analyzed.

**Discussion:**

By virtue of the direct comparison of clinically and economically relevant endpoints, the efficacy as well as efficiency of preoperative calcitriol prophylaxis of hypocalcaemia will be clarified. These results should be available 24 months after the first patient has been enrolled. The results will be used to inform a revised practice parameter guideline of whether or not to recommend preoperative calcitriol for all patients in whom total thyroidectomy is planned.

**Trial registration:**

Deutsches Register Klinischer Studien, DRKS00005615 (Feb.12.2016).

## Background

Surgery of the thyroid gland is one of the five most common surgical procedures in Germany, accounting for some 90000 operations per year [1]. Because subtotal thyroidectomy is no longer regarded the treatment of choice for multinodular goitre and Graves’ disease [2], the number of patients treated by total thyroidectomy has progressively increased, amounting to 47.9 % in 2011 [3]. This surgical approach aims to prevent recurrent disease and is supported by current guidelines, such as the national S2-guideline issued by the Work Group of the Scientific Medical Professional Societies [4]. However, postoperative symptomatic hypocalcaemia due to transient hypoparathyroidism is a frequent condition after total thyroidectomy, and is reported to occur in up to 54 % of patients [5]. Owing to the extent of resection in the case of total thyroidectomy, the viability of all four parathyroid glands may be endangered because of surgical trauma, and their function may be temporarily or permanently impaired. Risk factors for transient or permanent hypoparathyroidism after total thyroidectomy are higher age, female sex, Graves’ disease, need for parathyroid autotransplantation, inadvertent excision of parathyroid glands and low postoperative parathyroid hormone and serum calcium levels, as well as low preoperative serum 25-hydroxy vitamin D level [6].

Postoperative hypocalcaemia affects patients’ physical health and quality of life and causes a significant economic burden for the healthcare system. Acute hypocalcaemia may cause seizures or cardiac or digestive dysfunction, as well as phobic psychological disorders. Hypocalcaemic patients require continuous medical attention, frequent and more extensive biochemical tests and more medical treatment, including more medication. Moreover, a recent observational study reported the average length of hospital treatment of patients with postoperative hypocalcaemia to be increased by 2.2 days, compared with that of normocalcaemic patients [5]. Hence, the search for methods to reduce the incidence and severity of postoperative hypocalcaemia is of clinical, medical and economic relevance.

Despite ongoing research on the prevention of postoperative hypocalcaemia, its treatment is well established and uses oral calcium and vitamin D supplementation. Based on empirical evidence, Tartaglia *et al.* [7] were the first to show that routine postoperative administration of calcitriol and calcium salts significantly decreased the risk of severe postoperative hypocalcaemia. Indeed, low levels of vitamin D, as determined by preoperative testing, were shown to be an independent risk factor for postoperative hypocalcaemia [8], suggesting that correction of low vitamin D levels might be a useful measure to reduce postoperative hypocalcaemia rates.

Vitamin D metabolites and analogues are essential in the management of postsurgical hypoparathyroidism. The active form of vitamin D – calcitriol (1,25-dihydroxyvitamin D_3_) – is the preferred clinical option because of its potency and rapid onset and offset of action. Calcitriol regulates the expression of TRPV6, which is a calcium entry channel responsible for calcium absorption in the intestine [9], so that there is a time of onset of action of only some 1 or 2 days compared with 10–14 days for Vitamin D_3_ (cholecalciferol) [10].

We therefore hypothesized that preoperative administration of calcitriol would reduce the rate of hypocalcaemia after total thyroidectomy. Moreover, if postsurgical hypocalcaemia should occur, preoperative vitamin calcitriol prophylaxis should be helpful in reducing the time to manage this condition and thus the duration of hospital stay. So far, and to the best of our knowledge, studies to that effect are still missing.

### Aim of the study

The overall aim of this study is to evaluate the effect of an early onset of calcitriol supplementation on postoperative hypocalcaemia. This study is specifically designed to evaluate the effects of a preoperative short term administration of calcitriol prior to total thyroidectomy (intervention) in comparison with current standard clinical protocols of postoperative administration of calcitriol in only those patients who have postoperative hypocalcaemia (control group). Calcitriol will be administered according to well-established clinical protocols and no additional diagnostic interventions are intended, in order to reduce the likelihood of adverse events. This study is therefore planned as a post-marketing noninterventional, i.e., observational study. Although we consider HypoCalViD to be an observational trial rather than a prospective randomized controlled trial, because patients are randomly allocated to an interventional and a noninterventional arm prior to surgery, this trial may be attributed a ‘minimal-intervention clinical trial’ as recently defined by EU-directive number 536/2014 of 16 April 2014.

## Methods/design

### Trial population and eligibility criteria

HypoCalViD is a prospective, randomized, multicentre study (Fig. 1) involving patients with benign thyroid disease (Graves’ disease, multinodular goitre, hyperthyroidism) undergoing primary elective total thyroidectomy. Such patients will be eligible to participate after they have given their written informed consent. Patients with conditions that could potentially affect serum calcium levels, such as musculoskeletal diseases, hyperparathyroidism and medications known to affect calcium metabolism are excluded.

**Fig. 1 Fig1:**
[figure not shown]
Setup of the study

This multicentre study will be conducted in hospital departments with the required staffing levels and structural as well as scientific volume qualifications. Only hospital departments with a special interest in endocrine surgery and a working volume accounting for more than 100 total thyroidectomies per year, will be eligible to participate. The head surgeons of these departments must be members of the German Association of Endocrine Surgeons of the Deutsche Gesellschaft für Allgemein und Viszeralchirurgie.

### Sample size

The sample size has been calculated based on assumptions generated from a critical appraisal of current evidence. According to prior publications, 25 % of the patients in the control group can be expected to develop postsurgical hypocalcaemia as compared with 15 % of the patients in the intervention group. Assuming an α-level of 5 % and a power of 80 %, it is calculated that 500 patients must be recruited to obtain significant results. Assuming a cumulative drop-out rate of 10 %, 700 patients will have to be screened in order to obtain a total number of 600 patients for random allocation. Subsequently, it is expected that data obtained from 540 patients will be analyzed at primary endpoint. By using an adaptive study design, the number of patients will be re-evaluated after the first 270 patients have been treated, with complete follow-up.

#### Feasibility

A small number of high-volume providers will be eligible to participate in this study. As this study will take place only at high-volume centres chaired by highly specialized endocrine surgeons, we assume that the operation will be done or supervised by a specialist. Stratification, therefore, is done by centres rather than by surgeon. In 2013, these high-volume providers took care of some 2500 surgical cases. All of the potential study centres are active members of the German Association of Endocrine Surgeons and have been involved in clinical multicentre trials in the past. Given these facts, it was reasonable to assume the average recruitment rate with a minimum of 60 patients per year and per centre, resulting in an estimated recruitment phase of 24 months.

### Type of trial

This study is designed as a multicentre, parallel-designed, randomized, clinical, observational trial (minimal-intervention clinical trial).

### Randomization

Randomization to the treatment arm and the control group will be performed in a 1:1 ratio, stratified by each participating centre. Random allocation of patients will be dynamical. For the randomization procedure, the computer program ‘Random Allocation Software’ (Version 1.0.0) will be used; permuted block sizes will be 30 and 60.

### Intervention

The specific trial intervention consists of 0.5 μg calcitriol orally, twice a day for 3 days prior to surgery. The control therapy consists of any standard conventional hypocalcaemia therapy according to current guidelines or local clinical standards of the participating clinical centre and adherent to the implemented standards of the respective institution. Standard therapy is defined as the currently accepted and used treatment for this condition, based on the results of past research.

### Endpoint measures

#### Primary endpoint measure

The incidence of postsurgical hypoparathyroidism is defined as the primary endpoint measure. Postsurgical (transient) hypoparathyroidism is defined as the number of participants with a postoperative serum calcium concentration <2.1 mmol/l on any day of the postoperative hospitalization period. Since there is no evidence- or consensus-based definition of postoperative hypoparathyroidism based on calcium and parathyroid hormone cutoff levels, we defined postoperative hypoparathyroidism as calcium and parathyroid hormone levels below the normal range (Ca < 2.1 mmol/l), in line with expert opinion [11]. Application type, form and dosage of calcium and vitamin D administration therapy to achieve normocalcaemia will be recorded. Study parameters will be recorded before surgery, on postoperative days 1 and 2, and at discharge, as well as 30 ± 3 days following surgery.

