#### Secondary endpoint measures

Secondary endpoint measures comprise the overall duration of hospital stay, the number of days until restoration of normal serum calcium level, and hospital resource utilization, as well as quality of life and reported patient outcomes.

Duration of hospital stay will be documented according to hospital charts. Prior to and one month after surgery, patients will be asked to complete the well-established SF36 Quality of Life questionnaire [12] and a questionnaire constructed for the assessment of postoperative hypocalcaemia [13]. The number of days needed to adjust hypocalcaemia to a normal level (calcium level = 2.2 to 2.7 mmol/l) will also be assessed.

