Calcitriol will be given to the patients regardless of their vitamin D status, although prior evidence suggests that including patients only with a documented low vitamin D level would potentially increase the likelihood of a positive effect of calcitriol administration (the intervention) on both the primary and secondary outcome parameters. The main reason for not taking preoperative vitamin D levels into account is that this study aims at not interfering with the current standard of care or established guideline-oriented clinical management of patients with postoperative hypocalcaemia after thyroid surgery.

Although the assessment of vitamin D levels is recommended by guidelines addressing common problems of older people, such as osteoporosis, routine assessment of vitamin D is not yet established in clinical practice in Germany. In addition, determination of a patient’s vitamin D level incurs a minimum charge of €27.98 – with a potential for additional costs of €2.60 for taking the blood sample – while the calcitriol prophylaxis employed in this study proposal incurs an additional cost of less than €5 per patient. Because such a routine prophylaxis is considerably less costly and – given a positive outcome of this study – much easier to implement, the trial is likely to offer a realistic chance of optimizing treatment of patients undergoing thyroid surgery.

The primary endpoint measure is defined by total serum calcium level. Although ionized calcium level might be more specific in detecting hypocalcaemia, especially in the presence of malnutrition, ionized calcium is not a commonly used laboratory parameter during postsurgical follow-up of thyroid patients. We decided to ask for total calcium level only, as most hospitals and surgical departments make use of this parameter. Moreover, the observational nature of this trial intends not to interfere with the respective standard of treatment. Therefore, no additional parameters other than the individual trial sites’ ‘usual’ parameters were included.

Moreover, the majority of patients with elective benign thyroid surgery should not suffer from severe protein deficiency.

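### The primary endpoint counts a low calcium on any day of the stay, but the recording schedule has no point between postoperative day 2 and discharge

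*Protocol article*

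**What the plan says.** In the protocol article, under Primary endpoint measure, an event is a "postoperative serum calcium concentration <2.1 mmol/l on any day of the postoperative hospitalization period". The abstract gives an equally open window: "serum calcium of less than 2.1 mmol/l on any day during the postoperative course". The Primary endpoint measure section then sets the collection times: "Study parameters will be recorded before surgery, on postoperative days 1 and 2, and at discharge, as well as 30 ± 3 days following surgery".

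Under Secondary endpoint measures, time to recovery is also an endpoint: "The number of days needed to adjust hypocalcaemia to a normal level (calcium level = 2.2 to 2.7 mmol/l) will also be assessed". Hospital charts are named as a source for one item: "Duration of hospital stay will be documented according to hospital charts". The Discussion explains that the trial does not add to routine care: "no additional parameters other than the individual trial sites’ ‘usual’ parameters were included".

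Under Data analysis, the primary endpoint is compared by a Chi-square test. A log rank test with supportive Cox regression is planned for a secondary efficacy parameter that is not named.

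**The concern.** The endpoint window covers every day in hospital. The schedule covers days 1 and 2 and the day of discharge. Both are stated in the same section, so this is a mismatch within the article and not a detail left to another document.

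Two endpoints are affected. For the primary endpoint, a low value that first appears after day 2 and has resolved by discharge leaves no trace in the scheduled data. For days to normal calcium, a patient not yet normal on day 2 has no further scheduled value until discharge. If still not normal at discharge, the next value comes about a month after surgery.

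Missed events cost power. If sites differ in whether they enter other routine values, ascertainment of the primary endpoint also differs between sites.

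**Working it through.** **Step 1: which days are uncovered.** The scheduled in-stay values after surgery are day 1, day 2 and discharge day *d*. The uncovered days run from day 3 to day *d* − 1, which is *d* − 3 days when *d* is above 3 and none otherwise.

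- Discharge by day 3: no gap.
- Discharge on day 5: days 3 and 4 are uncovered.

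**Step 2: which patients are misclassified on the primary endpoint.** All three conditions must hold: at or above 2.1 mmol/l on days 1 and 2; below 2.1 on an uncovered day; at or above 2.1 at discharge. An invented example is 2.15 on days 1 and 2, 2.02 on day 3, and 2.20 at discharge on day 5. Anyone low on day 1, on day 2 or at discharge is counted correctly.

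**Step 3: days to normal (2.2 to 2.7 mmol/l).**

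- Low on day 1, normal on day 2: timed adequately.
- Not normal on day 2, normal at discharge: known only to lie between day 2 and discharge.
- Not normal at discharge: known only to lie between discharge and day 27 to 33. For discharge on day 3, that interval is 27 − 3 = 24 to 33 − 3 = 30 days.

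**Step 4: reproduce the planned size.** Inputs from Sample size and Randomization: 25% v 15%, alpha 5%, power 80%, 1:1 allocation. Sidedness is not stated; two-sided reproduces the figure. With pooled variance and no continuity correction,

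n per arm = [1.96·√(2·0.20·0.80) + 0.8416·√(0.25·0.75 + 0.15·0.85)]² / 0.10² = (1.1087 + 0.4724)² / 0.01 ≈ 250.

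The total is 500, as stated. The plan expects 540 analysed (600 × 0.90), or 270 per arm.

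**Step 5: power if a share m of events is missed equally in both arms.** The observed rates become 0.25(1 − m) and 0.15(1 − m). With p̄ their mean and d their difference,

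power = Φ{[d − 1.96·√(2p̄(1 − p̄)/270)] / √([p₁(1 − p₁) + p₂(1 − p₂)]/270)}.

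For m = 0: (0.10 − 1.96 × 0.03443)/0.03416 = 0.952, power 83.0%. For m = 10%: (0.09 − 1.96 × 0.03307)/0.03284 = 0.767, power 77.9%.

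| Share missed (assumed) | Observed rates | Power, 540 analysed | Total N for 80% power |
|---|---|---|---|
| 0% | 25% v 15% | 83.0% | 500 |
| 5% | 23.75% v 14.25% | 80.5% | 534 |
| 10% | 22.5% v 13.5% | 77.9% | 570 |
| 20% | 20% v 12% | 71.9% | 658 |
| 30% | 17.5% v 10.5% | 65.0% | 770 |

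**Step 6: unequal loss.** The planned difference is 10 points. Missing 10% of events in the control arm only gives 22.5% v 15%, a difference of 7.5 points. Missing 10% in the calcitriol arm only gives 25% v 13.5%, a difference of 11.5 points.

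**The case against.** The strongest reply is that the article lists when study parameters are recorded but does not say that nothing else is recorded. An any-day endpoint reads naturally as drawing on the hospital's routine values, and which laboratory results are transcribed is often a matter for the case report form. It is true that the schedule is not worded as exclusive. The article also never says that all in-stay calcium values are captured, and it names charts as the source for length of stay only. Even if full capture was intended, the text needs to say so.

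A second reply is that the gap may be small. This also stands in part. The discharge value is recorded, and only late-onset lows that resolve before discharge are missed. The Background's figure of 2.2 extra days for hypocalcaemic patients makes uncovered days plausible but does not size the gap, because it is a difference from normocalcaemic patients in another study. The documents give neither the absolute stay nor the timing of the lowest calcium.

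A third reply concerns the remedy. The trial is unblinded and follows local practice, so values after day 2 are driven by clinicians. If one arm is sampled more often, using every value finds more events in that arm. This stands, and the fix has to deal with it.

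Some stronger readings are tempting. A reader might infer that every low value after day 2 is lost, or that days to normal calcium simply becomes length of stay or about day 30. Neither follows: discharge values count, recovery by day 2 is seen, and the article nowhere dates recovery to the discharge or day-30 record. A reader might also infer that calcitriol merely delays the fall, so that lows are lost mainly in that arm and the benefit is overstated. The Background mentions calcitriol's rapid onset and offset together, as a reason for preferring it; it does not describe a delayed fall. Step 6 shows that the bias could go either way.

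**Conclusion.** The mismatch is real and should be resolved. Followed as written, the schedule cannot deliver the any-day definition for patients first low after day 2 and recovered by discharge, and it gives only an interval for time to normal in patients not normal by day 2.

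The size is unknown, because every missed share used here is an assumption. An equal loss of 5% leaves power at 80.5%, still above the planned 80%; 10% brings it to about 78% and 20% to about 72%. These figures rest on the planned rates, a two-sided 5% test and 270 analysed per arm. The direction of any bias from unequal loss cannot be told from the documents. The planned sample size is correctly calculated and is not in question.

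**What to change.** In Primary endpoint measure, state that every routine serum calcium value drawn during the stay is recorded from the hospital record with its date, and that the any-day endpoint is derived from all of these values. This needs no extra blood samples and fits the trial's aim of not adding to usual care.

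Alongside it:

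- Report the primary endpoint restricted to the scheduled points (days 1, 2 and discharge) as a sensitivity analysis.
- Report the number of calcium samples per patient by arm.
- Treat time to normal calcium as interval-censored, between the last value outside and the first value within 2.2 to 2.7 mmol/l.

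The cost is slightly more data entry and an interval-censored analysis of time to normal. The downside is possible differential sampling between arms, which the restricted analysis and the sample counts are there to check. Transcription also cannot supply a value for a day on which no blood was drawn.

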#### Secondary endpoint measures

Secondary endpoint measures comprise the overall duration of hospital stay, the number of days until restoration of normal serum calcium level, and hospital resource utilization, as well as quality of life and reported patient outcomes.

Duration of hospital stay will be documented according to hospital charts. Prior to and one month after surgery, patients will be asked to complete the well-established SF36 Quality of Life questionnaire [12] and a questionnaire constructed for the assessment of postoperative hypocalcaemia [13]. The number of days needed to adjust hypocalcaemia to a normal level (calcium level = 2.2 to 2.7 mmol/l) will also be assessed.

